## Abstract

**Background:**

Intracerebral hemorrhage (ICH) is a potentially devastating condition with elevated early mortality rates, poor functional outcomes, and high costs of care. Standard of care involves intensive supportive therapy to prevent secondary injury. To date, there is no randomized control study demonstrating benefit of early evacuation of supratentorial ICH.

**Methods:**

The Early Minimally Invasive Removal of Intracerebral Hemorrhage (ENRICH) Trial was designed to evaluate the minimally invasive trans-sulcal parafascicular surgery (MIPS) approach, a technique for safe access to deep brain structures and ICH removal using the BrainPath^®^ and Myriad^®^ devices (NICO Corporation, Indianapolis, IN). ENRICH is a multi-centered, two-arm, randomized, adaptive comparative-effectiveness study, where patients are block randomized by ICH location and Glasgow Coma Score (GCS) to early ICH evacuation using MIPS plus standard guideline-based management vs. standard management alone to determine if MIPS results in improved outcomes defined by the utility-weighted modified Rankin score (UWmRS) at 180 days as the primary endpoint. Secondary endpoints include clinical and economic outcomes of MIPS using cost per quality-adjusted life years (QALYs). The inclusion and exclusion criteria aim to capture a broad group of patients with high risk of significant morbidity and mortality to determine optimal treatment strategy.

**Discussion:**

ENRICH will result in improved understanding of the benefit of MIPS for both lobar and deep ICH affecting the basal ganglia. The ongoing study will lead to Level-I evidence to guide clinicians treatment options in the management of acute treatment of ICH.

**Trial registration:**

This study is registered with clinicaltrials.gov (Identifier: NCT02880878).

## Introduction

Intracerebral hemorrhage (ICH) accounts for 10–15% of all strokes and its prevalence continues to increase with an aging population. ICH-related early mortality rates range from 35 to 52% (1). Among survivors, only 10–25% return to functional independence, with an estimated annual cost of care and productivity losses of approximately 12.7 billion US dollars (2–5). Clinical outcomes following an ICH are negatively affected by the mechanical complications of mass effect leading to concomitant tissue infarction and intracranial hypertension. In addition, the hematoma in the brain parenchyma mediates a secondary inflammatory cascade.

An effective therapy for ICH patients has been elusive despite several well-designed clinical trials focused on surgical evacuation (6, 7), hemostasis augmentation (8), and blood-pressure reduction (9–11), among other interventions, all of which have failed to improve functional outcomes.

The role of surgery in the care of supratentorial ICH has been limited to life-saving clot evacuation, decompressive craniectomy, or a combination of these two procedures. Despite preclinical evidence supporting the role of hematoma evacuation on early correction of intracranial hypertension and prevention of secondary injury mechanisms, surgical intervention for supratentorial ICH remains unproven in randomized clinical trials (12).

Technology and technique development in support of minimally invasive surgery (MIS) has been encouraged by the hypothesis that prior randomized surgical trials failed to demonstrate benefit in part due to cortical and white matter tract injury incurred while accessing the clot with traditional techniques and tools. Indeed, surgical clot evacuation remains appealing based on the existing preliminary data, which continue to support the time-dependent pathophysiology of ICH, and that early removal of clot mitigates injury to surrounding tissue (13–15). Recent reports describing the safety of image-guided catheter placement for aspiration followed by infused thrombolytics in the MISTIE II trial have produced promising results supporting the premise of tissue preservation and the benefit of clot reduction (16).

Since the MISTIE approach was first described, multiple technological advances have occurred in diagnostic imaging, intraoperative frameless navigation, and navigable port-based minimally invasive access. The preliminary experiences reported by Labib et al. and Bauer et al. suggest that minimally invasive trans-sulcal parafascicular surgery (MIPS) is safe, prevents rebleeding, and maximizes clot evacuation (17, 18). In these studies, intervention occurred as early as 16 and 6.2 h, respectively, suggesting that MIPS may be safely performed while preserving eloquent white matter tracts and producing excellent clot reduction, without significant risk of hemorrhage recurrence, even when surgery is performed early.

To further evaluate this strategy, a randomized clinical trial was designed to assess the clinical benefit of a standardized MIS approach. The proposed MIPS approach was developed to provide atraumatic access, high-resolution visualization, and intraoperative tools for maximal clot evacuation and definitive hemostasis. In this article, we describe the design and methods for the Early Minimally Invasive Removal of Intracerebral Hemorrhage (ENRICH) trial and provide the rationale for the choice of design parameters.

## Methods and analysis

### Study objective

The primary objective of the ENRICH trial is to determine if early ICH evacuation using MIPS results in improved outcomes for patients with an ICH. The primary hypothesis is that MIPS will result in an improvement in the 180-day utility-weighted modified Rankin Scale (UWmRS) when compared to patients treated with standard guideline-based management. To address the primary objective, we have designed an adaptive clinical trial with a sample size between 150 and 300 subjects, with frequent interim analyses to determine if early stopping rules are met and if patient population enrichment per hemorrhage location should occur. Randomization between MIPS and standard management groups will be equal and patients will be block randomized by ICH location, anterior basal ganglia (ABG) vs. lobar location as well as Glasgow Coma Score (GCS) with a threshold for stratification <9 vs. ≥9. At each interim analysis, the enrollment scheme defined by hemorrhage location can be adapted based on the *a priori* enrichment plan.

Secondary aims of the study will evaluate the economic and clinical benefits, and the safety of MIPS compared to standard management. The clinical benefit of MIPS is thought to be a function of clot removal while minimizing white matter injury. Therefore, we will determine if the percent volume of ICH reduction is associated with improved UWmRS at discharge, 30, and 90 days between the treatment groups. The economic effect of MIPS for ICH will be evaluated by quantifying the cost per quality-adjusted life-year (QALY) gained through MIPS at 30, 90, 120, and 180 days. Safety of MIPS will be assessed: (1) by determining the effect of MIPS on mortality when compared to standard management at 30 days; (2) by assessing post-operative rebleeding associated with clinical deterioration following MIPS. Rebleeding will be defined by a growth in hemorrhage volume between an initial non-contrast head computed tomography scan (NCCT) and a follow-up NCCT obtained within 24 h of the index NCCT. Lastly, we will evaluate the impact of time from onset of symptoms to MIPS on the UWmRS.

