### Pre-randomization procedures

On arrival at the study hospital emergency department (ED), rapid evaluation and treatment will occur per routine including a physical assessment (GCS and National Institutes of Health Stroke Scale-NIHSS), NCCT, head CT angiogram, laboratory evaluation, and appropriate resuscitation (Figure 2). Participating neurosurgeons are instructed to contact the local Investigator on Call (IOC) for subject eligibility.

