### Study treatment

Subjects randomized to MIPS will have the intervention performed as close to the time of randomization as possible. Study protocol requires subjects to enter the OR within 24 h from last known normal (LKN), with a goal of arrival in the OR within 8 h. MIPS is to be performed in accordance with the study surgical manual (Supplementary Datasheet 1). All surgically randomized cases are video recorded, with the first two surgical cases from each site reviewed by the study's lead neurosurgeon (GP) to objectively assess adherence to the surgical protocol. Following surgery, care will follow the Clinical Standardization Guidelines (CSG) for management (Supplementary Datasheet 2).

In the standard treatment arm, subjects will be treated according to the CSG. The decision for surgical intervention with an external ventricular drain for CSF diversion or ICP control/monitoring, decompressive craniectomy, clot evacuation using traditional techniques, or both is left to the treating neurosurgeon. As traditional surgical techniques, such as decompressive hemicraniectomy, remain available to the treating team in the standard management arm, cross-over from this arm to MIPS is strictly not permitted.

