### Primary safety objective

The primary safety objectives will be evaluated by the rate of mortality and/or rebleeding at 30 days, which will be compared between the two groups using a Pearson's chi-square test and the difference in hemorrhage volume between index CT and 24-h follow-up CT, which will be compared between the two groups using a two-sided *t*-test (or Wilcoxon rank sum test if the normality assumption is violated).

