### Secondary endpoints

The secondary endpoints were selected to provide supportive information on safety and efficacy. These secondary endpoints include:

Postoperative rebleeding associated with deterioration following MIPS (no hypothesis test).ICU and in-hospital length of stay (two-sided *t*-test).mRS at discharge, 30 and 90 days (ordinal logistic regression; treatment as explanatory variable).Impact of percent ICH reduction with MIPS on mRS at 180 days (ordinal logistic regression; %ICH reduction as explanatory variable).Impact of end-of-treatment (EOT) volume with MIPS on mRS at 180 days (ordinal logistic regression; EOT volume as explanatory variable).Proportion of patients with mRS at 180 days equal to 0, 1, 2, or 3 (chi-square test).Ordinal mRS at 180 days (Wilcoxon rank sum test).Overall survival through 180 days (log-rank test and Cox proportional hazards model).

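### Measured from the pre-randomization CT, the volume-change safety test captures clot removal, and rebleeding after evacuation is masked or missed

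*Protocol article*

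**What the plan says.** Under Study objective, one safety aim is to be met "by assessing post-operative rebleeding associated with clinical deterioration following MIPS". The definition follows at once: "Rebleeding will be defined by a growth in hemorrhage volume between an initial non-contrast head computed tomography scan (NCCT) and a follow-up NCCT", the second scan being "a follow-up NCCT obtained within 24 h of the index NCCT". The first scan belongs to the emergency work-up. Under Pre-randomization procedures, "rapid evaluation and treatment will occur per routine including a physical assessment (GCS and National Institutes of Health Stroke Scale-NIHSS), NCCT, head CT angiogram" are listed, and Table 2 requires a pre-randomization CT with an ICH volume of 30 to 80 ml.

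The Primary safety objective names two between-arm comparisons:
- "the rate of mortality and/or rebleeding at 30 days", by Pearson's chi-square test;
- "the difference in hemorrhage volume between index CT and 24-h follow-up CT, which will be compared between the two groups", by t-test or Wilcoxon test.

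The Secondary endpoints add "Postoperative rebleeding associated with deterioration following MIPS (no hypothesis test", with no definition or baseline scan of its own. On the timing of surgery, the Study treatment section says: "Study protocol requires subjects to enter the OR within 24 h from last known normal (LKN", with a goal of 8 h. Table 1 marks rebleeding in the column headed within 24 h of last known normal (LKN).

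**The concern.** The stated aim is to detect bleeding after the operation, but the yardstick is the haematoma before it. MIPS is designed to remove as much clot as possible, so in an operated patient the follow-up volume is the residual plus any new bleeding. Set against the full original clot, even a sizeable rebleed can register as shrinkage. In an unoperated control the same comparison measures natural expansion directly.

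Rebleeding is a central procedure-specific harm. A primary safety comparison that answers mainly to the success of evacuation could be read as reassurance about bleeding when it carries little information on it.

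**Working it through.** The document gives no rate, power or sample size for the safety tests, so there is no figure to reproduce. The check is algebra on the definition, followed by an illustration on stated assumptions.

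**1. Which scan is the baseline?** The text says initial and index, not pre-treatment. The Primary safety objective applies the index CT to both groups, and unoperated controls have no post-operative scan. The NCCT sits in the pre-randomization work-up, and no post-operative baseline for rebleeding is defined anywhere. Pre-randomization is the reading the text supports.

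**2. Size of rebleed needed to count.** Let V be the index volume, f the evacuated fraction and g the rebleed volume. Follow-up volume is (1 − f)V + g, so growth over V requires g > fV. V comes from Table 2; f is not given and is assumed.
- f = 0.80: 0.80 × 30 = 24 ml, 0.80 × 80 = 64 ml.
- f = 0.70, smallest clot: 0.70 × 30 = 21 ml. f = 0.95, largest clot: 0.95 × 80 = 76 ml.
- Example: a 50 ml clot evacuated by 80% leaves 10 ml. A 30 ml rebleed brings it to 40 ml, below 50 ml, and is recorded as no growth.

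**3. Illustration for the rebleeding component.** Assume V uniform on 30 to 80 ml, g uniform on 5 to 40 ml, every MIPS patient evacuated before the second scan, and no control evacuated. The share of rebleeds recorded is P(g > fV):
- f = 0.5: the threshold is uniform on 15 to 40 ml, mean 27.5, so (40 − 27.5)/35 = 0.357.
- f = 0.7: the threshold is uniform on 21 to 56 ml, so (19²/2)/(35 × 35) = 0.147.
- f = 0.9: the threshold is uniform on 27 to 72 ml, so (13²/2)/(35 × 45) = 0.054.

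| True rebleeding, MIPS / control | Recorded in MIPS at f = 0.5 / 0.7 / 0.9 | Recorded in control |
|---|---|---|
| 10% / 10% | 3.6% / 1.5% / 0.5% | 10% |
| 20% / 10% | 7.1% / 2.9% / 1.1% | 10% |

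Even with true rebleeding doubled under MIPS, the recorded rate stays below control.

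**4. Volume test.** On the same assumptions mean V is 55 ml and mean g is 22.5 ml. The expected difference (MIPS − control) is −55f + 22.5(p_MIPS − p_control), where p is the true rebleed rate.
- Equal rebleeding: −27.5, −38.5 and −49.5 ml at f = 0.5, 0.7 and 0.9. Simulated SDs are 9.1, 10.3 and 11.8 ml, and power with 75 per arm (two-sided 0.05) is essentially 100%.
- 20% against 10%: the excess bleeding moves the result by 22.5 × 0.10 = 2.25 ml, to about −25, −36 and −47 ml.
- Measured from a post-operative scan instead, the differences are 0 ml and about +2.3 ml, so the excess becomes visible.

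If only a share q of an arm is evacuated before the second scan, the evacuation term becomes −55(q_MIPS f_MIPS − q_control f_control). With q_MIPS = 0.5, f = 0.5 and no control evacuated it is −13.75 ml: smaller, but still an evacuation effect.

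**5. The window.** If the index CT is t hours after LKN and OR entry s hours after LKN, the last admissible follow-up CT is t + 24 − s hours after OR entry. With t assumed at 1 to 6 h, this is 17 to 22 h at s = 8 but only 1 to 6 h at s = 24, operating time included. A follow-up CT taken earlier may precede surgery. In that patient evacuation masks nothing, but post-operative rebleeding is not observed at all.

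**6. Time frames side by side.** Within 24 h of the index NCCT (Study objective), at 30 days (Primary safety objective) and within 24 h of LKN (Table 1). These are three different windows for one event.

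**The case against.** The strongest reply is that only part of the safety assessment is affected. A reader might infer that both primary safety comparisons favour MIPS by construction. The documents do not support that for the composite: 30-day mortality depends on no CT, the Introduction cites early ICH mortality of 35 to 52% (in a population not selected as this trial's is), and deaths may dominate. The rates in the working are for rebleeding alone; the composite was not computed. This objection stands.

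A reader might also infer that the harm would go unseen. Under Safety monitoring the DSMB receives group comparisons of rebleeding, haemorrhage expansion, surgical complications and other SAEs, and a medical monitor reviews every SAE. That weakens the inference, but these routes supply no other definition and do not repair the two tests.

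The absence of a minimum growth is not a fault here. It might be argued that measurement noise alone would label many stable controls as growing, but a threshold is detail that an analysis plan may set, and the aim's tie to clinical deterioration may exclude noise. Nor does the and/or wording of the composite rule out separate reporting.

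Finally, controls may have clot evacuated by traditional techniques (Study treatment; Rationale for preventing cross over to MIPS). This narrows the asymmetry and means such controls are masked too. It does not make the measure valid.

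**Conclusion.** The concern holds in a bounded form. As written, the index-to-24-h volume comparison measures evacuation rather than safety. The definition also records a post-operative rebleed only if it exceeds the volume removed: 24 to 64 ml at an assumed 80% evacuation, 21 to 76 ml over 70 to 95%. The threshold fV follows from the definition for any evacuation between the scans. That the between-arm bias favours MIPS requires more clot to be removed before the second scan in that arm than in controls. The recorded rates and volume differences also rest on the assumed evacuation fractions, rebleed sizes and rebleed rates.

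The rebleeding component of the composite is biased towards MIPS. The mortality component is not, so the net effect on the composite is diluted and unquantified. Masking and missing apply to different patients, according to whether the follow-up CT comes after or before surgery, and the document does not allow the split to be estimated. The UWmRS primary analysis and the stopping rules are not affected.

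**What to change.** - In operated patients of either arm, define rebleeding as growth from the first post-operative CT to later CTs, with the window counted from surgery. End-of-treatment volume is already needed for a secondary endpoint.
- In non-operated patients, measure expansion from the index CT.
- Apply the same growth criterion to both groups of patients.
- Report index-to-24-h volume change as degree of evacuation and remove it from the safety tests.
- Reconcile the three rebleeding time frames in the Study objective, the Primary safety objective and Table 1.

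The cost is mainly wording and re-reading of scans, with three real limits. Bleeding before the first post-operative CT is absorbed into the baseline. Imaging is collected only as done in routine care (Post-randomization in-hospital assessment), so patients with a single post-operative CT give no growth measurement; their number should be reported by arm. Natural expansion in unoperated patients is also not the same event as post-operative rebleeding, so the between-arm comparison needs that caveat.

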### Study design and method

ENRICH is an adaptive, two-arm, randomized comparative effectiveness study, where eligible patients are block randomized by ICH location (ABG vs. lobar) and GCS to early ICH evacuation using the MIPS approach plus standard management vs. standard guideline-based management alone. Scheduled interim analyses, beginning after 150 patients have been enrolled, will guide the adaptive sample size and study enrichment (Figure 1). A maximum of 300 subjects will be enrolled.

**Figure 1 F1:**
[figure not shown]
Study flow chart.

All randomized subjects are to be treated according to the study protocol, clinical standardization guidelines, and MIPS surgical standardization guidelines. Subjects are followed for 6 months or death (Table 1).

**Table 1 T1:** SPIRIT figure.

	**Study period**								
	**Enrolment**	**Allocation**	**Post-allocation**						**Close-out**
			**Pre-discharge**		**Post-discharge**				
**Timepoint**	*t* _1_	*t* _2_	*t*_3_ = **within 24 h from LKN**	*t*_4_ = **within 7 days from allocation**	*t*_5_ = **discharge**	*t*_6_ = **30 days**	*t*_7_ = **90 days**	*t*_8_ = **120 days**	*t*_9_ = **180 days**
**ENROLMENT**									
Physical assessment, NCCT, CT angiogram, lab, appropriate resuscitation	x								
Eligibility screen	x								
Informed consent	x								
Allocation		x							
**INTERVENTIONS**									
MIPS			x						
Standard treatment			According to CSG						
**ASSESSMENTS**									
Neurologic evaluation, lab, neuroimaging, CSG checklist									
ICH reduction in association with improved UWmRS					x	x	x		x
Economic effect: QALY						x	x.	x	x
Adverse event monitoring	x				x	x	x	x	x
Safety: mortality									
Safety: rebleeding			x						
mRS	x					x	x		x
HUI						x	x	x	x
NIHSS and GCS	x			x	x				x

### Pre-randomization procedures

On arrival at the study hospital emergency department (ED), rapid evaluation and treatment will occur per routine including a physical assessment (GCS and National Institutes of Health Stroke Scale-NIHSS), NCCT, head CT angiogram, laboratory evaluation, and appropriate resuscitation (Figure 2). Participating neurosurgeons are instructed to contact the local Investigator on Call (IOC) for subject eligibility.

**Figure 2 F2:**
[figure not shown]
Subject flow chart.

The IOC will review eligibility criteria and the patient's clinical information (Table 2). Once the patient meets eligibility criteria and informed consent has been obtained from the patient or legally authorized representative, the subject may be randomized using the central electronic data capture (EDC) portal.

**Table 2 T2:** Inclusion and exclusion criteria.

Study inclusion criteria	• Age 18–80 years • Pre-randomization head CT demonstrating an acute, spontaneous, primary ICH • ICH volume between 30 and 80 ml as calculated by the ABC/2 method • Study intervention can reasonably be initiated within 24 h after the onset of stroke symptoms. If the actual time of onset is unclear, then the onset will be considered the time that the subject was last known to be well • Glasgow Coma Score GCS 5–14 • Historical Modified Rankin Score 0 or 1
Study exclusion criteria	• Ruptured aneurysm, arteriovenous malformation (AVM), vascular anomaly, Moyamoya disease, venous sinus thrombosis, mass or tumor, hemorrhagic conversion of an ischemic infarct, recurrence of a recent (<1 year) ICH, as diagnosed with radiographic imaging • NIHSS <5 • Bilateral fixed dilated pupils • Extensor motor posturing • Intraventricular extension of the hemorrhage is visually estimated to involve >50% of either of the lateral ventricles • Primary thalamic ICH • Infratentorial intraparenchymal hemorrhage including midbrain, pontine, or cerebellar • Use of anticoagulants that cannot be rapidly reversed • Evidence of active bleeding involving a retroperitoneal, gastrointestinal, genitourinary, or respiratory tract site • Uncorrected coagulopathy or known clotting disorder • Platelet count <75,000, INR >1.4 after correction • Patients requiring long-term anti-coagulation that needs to be initiated <5 days from index ICH • End stage renal disease • Patients with a mechanical heart valve • End-stage liver disease • History of drug or alcohol use or dependence that, in the opinion of the site investigator, would interfere with adherence to study requirements • Positive urine or serum pregnancy test in female subjects without documented history of surgical sterilization or is post-menopausal • Known life-expectancy of <6 months • No reasonable expectation of recovery, DNR, or comfort measures only prior to randomization • Participation in a concurrent interventional medical investigation or clinical trial • Inability or unwillingness of subject or legal guardian/representative to give written informed consent • Homelessness or inability to meet follow up requirements

